### **D.2.3 SUSTAINMENT: Evaluation of GC-CCP implementation and maintenance process and outcomes**

After implementing GC-CCP with research enrolled index participants in the first 6 months of implementation to evaluate effectiveness, clinic staff will take over all aspects of implementation during the Sustainment phase (2.5 years). The study team will transition the training and supervision of peer facilitators to clinic providers. This phase is important to (a) fully understand implementation processes, facilitators of, and barriers to real-world implementation of GC-CCP (without research staff); (b) to study sustainability of GC-CCP (as well as CC prevention advocacy and CC screening) when GC-CCP is fully implemented by clinic staff; and (c) to prepare the clinics to maintain GC-CCP into the future, if it is found to be cost-effective in the RCT.

**Identifying and training clinic staff to supervise GC-CCP.** The study team will work with the clinics to identify staff to serve as supervisors for the Sustainment phase. The selected staff member will likely vary from site to site based on variability in staff composition and skill sets, but female counselors and nurses are suitable, if they have experience supervising other personnel. The peer facilitators will be identified and trained at the start of the Implementation phase (see D.2.2), but there is likely to be some turnover and need for training of new facilitators at some point during the 2.5 years of Sustainment. The clinic staff who will train and supervise the peer facilitators will be identified at the start of the RCT, so that they can participate in the initial training of facilitators as a co-trainer, receiving mentorship from the study team trainers and supervisors; she will also shadow [name] and [name] as they carry out supervision (including completion of fidelity rating forms after observing the implementation of sessions), in order to receive mentorship in this role. In the initial supervision sessions conducted by the staff member in the Sustainment phase, either [name] or [name] will attend twice a month for 3 months to provide continued mentorship. Supervision in this phase will be held after each session for the first group they oversee, followed by after every other session for successive groups.

**RE-AIM framework outcomes** will be assessed to evaluate GC-CCP implementation. Effectiveness of increasing CC screening (primary RCT outcome) will be based on chart data from enrolled alter participants. Reach in terms of how many women engage in GC-CCP and CC prevention advocacy will be assessed using chart data from CC screened clients, and survey data from enrolled index and alter participants, respectively. Semi-structured interviews and surveys with clinic staff (directors/managers, providers) and clients; supervisor ratings of facilitators (fidelity); and clinic budget ledgers (cost), will be used to assess EPIS constructs.

**Table 2. RE-AIM Outcomes**

| Outcome                                                                                      | Operationalization                                                                                                                                                                                                                                                                                                                                                                                                     | Data Source & Study Phase                                                                                                                                                                                                          |
|----------------------------------------------------------------------------------------------|------------------------------------------------------------------------------------------------------------------------------------------------------------------------------------------------------------------------------------------------------------------------------------------------------------------------------------------------------------------------------------------------------------------------|------------------------------------------------------------------------------------------------------------------------------------------------------------------------------------------------------------------------------------|
| Reach (CC screened women)                                                             | a) Proportion and characteristics (e.g., age, HIV status) of CC screened women who enroll in GC-CCP; and attend >3 sessions
Benchmark of success will be at least 15% of CC screened women annually who receive over half of sessions, based on Diffusion of Innovation theory, which posits that ~15% of a target group should be exposed for optimal population diffusion of information  | Data (enrollment, attendance dates) collected by clinic staff and added to medical chart (Implementation and Sustainment)                                                                                                          |
| Reach (CC screened women and their alters)                                            | b) Proportion and characteristics of research enrolled women who receive GC-CCP (i.e., index participants) who engage in advocacy
c) Proportion and characteristics of research enrolled alters who received advocacy from index participant
d) Proportion and characteristics of research enrolled alters who engage in advocacy with other alters                                                              | Survey data collected during RCT; intervention vs control comparison (Implementation)                                                                                                                                              |
| Effectiveness (alters)                                                                | Proportion of previously unscreened alters who get screened for CC,                                                                                                                                                                                                                                                                                                                                                    | Med chart (intervention vs control group in RCT; Implementation)                                                                                                                                                                   |
| Adoption (Clinic staff)                                                               | Clinic staff integrate GC-CCP (i.e., extent to which staff identify, train, and supervise peer facilitators, recruit clients, conduct sessions):

 
Proportion of staff who report recruiting clients for GC-CCP
 
Extent to which staff supervisor carries out weekly supervision of peer facilitators conducting GC-CCP sessions
 
                            | Twice yearly survey of clinic staff implementation activities (Sustainment)
Clinic staff supervisor fidelity forms (Sustainment)                                                                                                |
| Implementation (Fidelity)                                                             | Fidelity: Intervention facilitated as prescribed in manual (75% of session topics facilitated with fidelity across sessions)                                                                                                                                                                                                                                                                                           | Fidelity ratings (based on independent observations by 2 team members; Implementation & Sustainment)                                                                                                                               |
| Implementation (Perceptions of Implementation and Sustainment; EPIS domains)          | a) Perceived acceptability (satisfaction with GC-CCP) (EPIS Innovation)
b) Appropriateness (perceived fit/compatibility of GC-CCP with current practices) (EPIS Innovation & Inner Context factors)
c) Feasibility (extent to which GC-CCP can be successfully conducted by clinics staff) (EPIS Innovation & Inner Context factors)
d) Other barriers to and facilitators of implementation                  | Semi-structured interviews with stakeholders (policy, clinic, and client levels); (Implementation & Sustainment)
Brief surveys with health care providers, using adapted measures  (Implementation & Sustainment) |
| Implementation (Adaptation)                                                           | Documentation of adaptations and recommendations needed to promote and sustain implementation                                                                                                                                                                                                                                                                                                                          | Semi-structured interviews (clinic staff) (Implementation & Sustainment)                                                                                                                                                           |
| Implementation (Cost)                                                                 | Cost of implementation strategy                                                                                                                                                                                                                                                                                                                                                                                        | Clinic cost ledger (e.g., staff salaries, materials, space rental) (Sustainment)                                                                                                                                                   |
| Maintenance (assessed in "Sustainment" Phase only, last 2.5 years of data collection) | Implementation maintained over 2.5 years (i.e., GC-CCP conducted with at least 15% of women screened for CC; may be revised based on Implementation Phase evaluation)                                                                                                                                                                                                                                                  | Clinic records of GC-CCP implementation and client engagement (Sustainment)                                                                                                                                                        |
|                                                                                              | Supervision support for peer facilitators maintained over 2.5 years                                                                                                                                                                                                                                                                                                                                                    | Completed fidelity forms by clinic supervisor (Sustainment)                                                                                                                                                                        |
|                                                                                              | Women receiving the intervention sustain advocacy 12-months post GC-CCP participation                                                                                                                                                                                                                                                                                                                                  | Index client survey during RCT (Implementation & Sustainment)                                                                                                                                                                      |

**Medical chart abstraction.** We will use medical chart abstraction to assess Effectiveness (Implementation) and Reach (Sustainment). At the beginning of the RCT (Implementation Phase), we will work with the clinic to add a field to the client visit form to record referral source for CC screening (e.g., healthcare provider, another client, with names recorded); and if relevant, RCT enrollment (and date) and participation in GC-CCP (dates of sessions attended). Data on referral source will be checked for names of GC-CCP participants. From these data, we will determine Effectiveness (along with survey and chart data from enrolled alter participants) and Reach as operationalized in Table 2. Note that we have previously worked with Ugandan public and private healthcare facilities to add implementation variables to the medical chart, by creating brief hard copy forms or registries for clinic staff to complete, that can be linked with patient medical records.

**Survey data (index and alter participants).** Follow-up survey data from enrolled index and alter participants will be collected during the RCT; these data will inform Maintenance in terms of sustained engagement in CC prevention advocacy (during the Sustainment phase), as noted in Table 2.

**Semi-structured interviews.** We will assess implementation qualitatively with semi-structured interviews with clinic staff who are involved in CC screening and GC-CCP (e.g., clinic manager, GC-CCP peer facilitator, CC screener/treater). We will interview 20 staff (5 per clinic) at a private space at the clinic at the beginning of Sustainment, followed by 15 and 30 months later (ideally, all with the same staff), to complement the quantitative outcomes in helping to understand the implementation process. Staff will be assured of confidentiality and that their responses will not be shared with others at the workplace. We will use the interview guide developed for the Preparation Phase, revising questions as needed to ask about current (vs future) practices and adding probes about specific barriers that emerged in prior interviews, to assess changes in barriers over time. Such an iterative process allows for a deeper understanding of both the past and the present. We also will ask what resources are needed to sustain CC screening and GC-CCP.

**Client focus groups.** Based on medical chart data on GC-CCP participation and CC screening referrals, a random sample of clients who participate in GC-CCP, and a random sample of CC screened alter clients who state that they were referred by a peer who attended GC-CCP, will be asked to participate in one of two focus groups per site. Selected women will be stratified by age (age 25-35 vs. 36-49). Client participants will be referred by clinic staff to the study team for consent processes. Examples of questions to be asked of GC-CCP participants include, *How easy or challenging was it for you to engage with the training sessions (follow up: time of day, getting to training location, support from partner)? How useful was the content of the training? How much were your questions about disclosure [advocacy] addressed? How much, if at all, do you think the sessions increased your advocacy to other women?* Examples of questions to be asked of alters include, *Following the advocacy you received, what additional questions about CC screening do you have? How much were your questions about CC screening addressed? How would you describe the process of getting screened for CC? How much, if at all, do you think the advocacy you received affected your decision to get screened? How much, if at all, are you motivated to advocate as well to other women? Why/why not?*

**Survey data (clinic staff).** To complement the qualitative data on implementation and sustainability factors, we will collect brief survey data from clinic staff once at the beginning and once at end of the 30-month Sustainment phase. These data will include adapted survey items from three companion measures focused on the fit of GC-CCP with the clinic operations (e.g., “I welcome GC-CCP into the clinic,” “GC-CCP is a good fit with clinic practices,” and “It is possible to offer GC-CCP,” from 1=completely disagree to 5=completely agree). The questions will be tailored to the Ugandan clinic contexts during the Preparation stage of the project.

To assess Adoption, clinic staff will be given a quarterly anonymous brief survey to assess if they helped to implement GC-CCP and if so, the extent to which they performed key activities (e.g., identification and recruitment of CC screened clients to participate in GC-CCP; training or supervision of facilitators). A secure anonymous survey link will be emailed to providers, or given a hard copy to complete and insert into an envelope. We will convene clinic providers and leadership quarterly to assess implementation challenges (re. CC screening and GC-CCP) that are raised in the surveys or during the meeting, and how to address them.

**Qualitative analysis** methods will be similar to the Preparation phase (D.2.1). A longitudinal qualitative analysis will compare themes within and across timepoints to determine change in barriers over time (e.g., using summative analytic memos about themes at each timepoint). We will triangulate complementary data collected from medical charts, semi-structured interviews and brief clinic surveys on CC screening uptake using a mixed methods approach. E.g., if we find high uptake of GC-CCP among CC screened women (with >3 sessions attended), we will use the qualitative data to help explain why women found the intervention to be acceptable (e.g., that they enjoyed learning new skills for advocacy). Conversely, if we find that women are not engaging in advocacy, we may determine an explanation from the qualitative interview data (e.g., high stigma).

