**Game Changers for CC Prevention (GC-CCP).** GC-CCP draws on theories of network diffusion, cognitive consistency, and social influence, which posit that behavior change can be initiated by a few and diffused to others through modeling, advocacy, and shifts in social norms. GC-CCP uses 7 sessions to empower CC screened women to act as change agents for CC screening in their social networks. **Session 1** addresses fears and concerns related to CC risk and use of self-compassion and peer support to overcome these fears. **Session 2** focuses on decision making for sharing one's personal CC screening experience, and how to initiate disclosure and conversations about CC. **Session 3** builds self-efficacy for CC risk management so that one's own behavior (e.g., recognizing signs of CC risk and seeking CC-related health services as needed; periodic VIA screens) coincides with the behavior they encourage in others, as well as learning CC facts and myths to facilitate accurate CC screening advocacy. **Session 4** demonstrates how one's social network can serve as a tool for dissemination of CC prevention advocacy and knowledge. **Sessions 5 and 6** build CC advocacy skills: communication skills (e.g., reflective listening, paraphrasing, open ended questions), and how to start and sustain conversations about CC. Participants learn to identify alters in their network who may be prime targets for advocacy and transfer of information and norms throughout the network (e.g., well connected to other alters; are "bridges" between two distinct groups of alters). **Session 7** inspires commitment to ongoing CC advocacy through peer solidarity and support. The 2-hour, weekly sessions will be conducted in Luganda using a structured manual, and group format to facilitate: sharing of experiences to build solidarity, support, and motivation among participants; group problem solving and role playing to build skills and self-efficacy; and homework between sessions to practice new skills and generate experiences to be processed in the sessions.

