**D2.2.1 Multi-site RCT of CC-CCP.** At all 4 sites, 40 women screened for CC in the past year will enroll as index participants (n=160), with 20 randomly assigned to the intervention, and 20 to a wait-list usual care control. Individual randomization entails contamination risks, but statistical models suggest  $\geq 30\%$  of the control arm must receive the equivalent of a full-strength intervention for meaningful contamination. We decided against an attention control, because attention paid to intervention (index) participants would not impact alter behavior (primary outcome), and its policy implications would be less clear. The intervention arm will be divided into 2 groups of 10 (balanced on ages 25-35 and 36+) for receipt of the intervention. The control arm receives the intervention after the 12-month follow-ups. Each index participant will recruit up to 3 alters (total= ~440 alters; referred to as 1st degree alters) with no history of CC screening. All index and 1st degree alter participants will be followed up at months 6 and 12. At month 6, 1st degree alters will recruit up to 2 of their own alters (2nd degree alters; total= ~800) who they report targeting with advocacy and thereafter getting screened for CC; 2nd degree alters will be administered a single, brief phone interview.

**Eligibility criteria:** *Index participants:* female, age 25+ (the lower limit for recommended CC screening), screened for CC in past year (clinic records), and no advanced stage disease (12-month follow-up is feasible). *1st degree alters:* female, age 25+, and report no CC screening history. *2nd degree alters:* female and age 25+.

**Recruitment** of index and 1st degree alters will span 8 weeks (5 index and 14 alters per week) at each site. Clinic staff will contact eligible women who have been screened for CC in the past year to inform them of the study; if interested, the site coordinator will perform consent processes and formal eligibility screening. Eligible women who enroll will complete the baseline survey, followed by randomization as an index participant.

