**1st degree alters:** The site coordinator will use the social network assessment within the baseline survey of each index to randomly select (using a random number table) 5 alters who know the participant's CC screening experience (or as many as there are if < 5) and ask the index if she is comfortable recruiting 3 of these alters. The index will be asked to call each selected alter at the end of their baseline interview to describe the study in the presence of the coordinator (or later in private, if she prefers), who will schedule a study visit for the alter. If an alter refuses or cannot be reached, a replacement will be randomly chosen from the original list of 5 alters.

**2nd degree alters:** The site coordinator will use the social network assessment in the month 6 survey of each 1st degree alter to randomly select 4 alters (or as many as there are if < 4) who the alter reports targeting with CC screening advocacy and thereafter was screened for CC. A similar process as described above for 1st degree alters, will be used to recruit and enroll 2nd degree alters. The coordinator will obtain verbal consent from the 2nd degree alter over the phone and the complete a brief 15-minute phone survey.

**Assessment schedule:** Surveys will be administered at baseline, month 6 and month 12 for index and 1st degree alters, and 2nd degree alters will be surveyed only once (at month 6 assessment of 1st degree alters). Participants will receive 30,000 Ush (~\$8) per assessment, except 2nd degree alters who will receive 10,000 Ush (via mobile money). To limit attrition, we will collect tracking information (phone numbers and mapped addresses), including contacts for family/friends with whom they have frequent contact. Clinic staff will help us track clients we have difficulty reaching. In the pilot, >96% of index and alters were retained at month 6.

**Measures:** Survey assessments for index and 1st degree alter participants will be interviewer-administered in Luganda using Network Canvas software, last ~ 75 minutes, and include a social network assessment. CC screening and treatment utilization will be verified with medical chart data.

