**Social network assessment:** The participant will list 10 female alters (which is adequate for structural and compositional variability) with whom they interact most. For each listed alter, we will gather information to assess *network composition* (e.g., age, relation to respondent, history of CC screening and treatment; knowledge of respondent's CC screening experience). In the index survey only, we will ask how if each alter knows each other alter to assess *network structure* (e.g., density); this section is time consuming, so given the large number of alter participants, alters will not complete this survey component. Research questions related to this section [e.g., do denser networks promote more CC screening within the network) will be addressed with index participant data. To assess CC advocacy and perceived effects, from the perspective of both the index and alter, we will ask the participants if they have engaged in CC screening advocacy (separate items for discussed, encouraged, gave info, gave direct support, and frequency) with the specific alter in the past 6 months, and any perceived resulting action (e.g., alter was screened). At follow-up, we will determine whether listed alters are the same or unique from those listed at baseline, to facilitate longitudinal analyses of alter data.

**Phone assessment of 2nd degree alters** will assess background characteristics, receipt of CC screening and treatment services, CC knowledge, receipt of CC screening advocacy from referring 1st degree alter, engagement in CC prevention advocacy (general), number of alters engaged in CC screening advocacy with, and the number of these alters perceived to have been screened for CC following this advocacy.

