## **F. DATA SAFETY AND MONITORING PLAN**

### **I. Description of Study and Study Data**

This study is a partnership among RAND Corporation ([name] and [name], MPIs), Makerere School of Public Health ([name], MPI), African Palliative Care Association, Rays of Hope Hospice Jinja, and Indiana University at Bloomington. We will conduct a hybrid implementation-effectiveness randomized controlled trial (RCT) of *Game Changers for Cervical Cancer Prevention (GC-CCP)*, a 7-session peer-led group intervention that aims to empower and mobilize women who have screened for cervical cancer (CC) to be agents for CC screening and prevention in their social networks. For the RCT, we will recruit 160 screened women (index participants) across 4 clinics, randomizing 80 to the intervention and 80 to the usual care control condition. Each index participant will be asked to recruit up to 3 social network members (1st degree alters) who have never screened for CC to complete assessments (~440 total based on average of 2.75 alters recruited per index participant, 220/arm) over 12 months, to test intervention effects on alter uptake of CC screening. All participants will complete surveys at baseline, and 6- and 12-months post-baseline. At the

month 6 follow-up, first degree alters will be asked to recruit up to 2 of their social network members (2nd degree alters; ~ 800 total). Surveys of index and alter participants will include questions about CC screening, CC knowledge, CC stigma, and engagement in CC prevention advocacy. Data on alter CC screening and treatment will be extracted from medical records. All data will be collected and stored at the participating clinic sites initially, and then transferred to Makerere University School of Public Health; de-identified data will be transferred to RAND for data management and analysis.

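### Table 2 promises advocacy sustained 12 months after GC-CCP participation, but its only source, the RCT index survey, ends 12 months after baseline, at most about 10.6 months after the last session

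*Protocol*

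**What the plan says.** Table 2 (RE-AIM Outcomes, section D.2.3) has three Maintenance rows. The third reads "Women receiving the intervention sustain advocacy 12-months post GC-CCP participation", and its data source is "Index client survey during RCT (Implementation & Sustainment". The paragraph on index and alter survey data after the table confirms that the RCT follow-up surveys are what inform this part of Maintenance.

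The survey clock is set elsewhere. The assessment schedule in D.2.2.1 states "Surveys will be administered at baseline, month 6 and month 12 for index". Section F, part I, fixes the origin: "All participants will complete surveys at baseline, and 6- and 12-months post-baseline".

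Training starts after that origin. The recruitment paragraph in D.2.2.1 states "Eligible women who enroll will complete the baseline survey, followed by randomization as an index participant". The Dose row of the implementation-strategy table in D.2.2 gives seven weekly sessions. Controls receive GC-CCP only once the 12-month follow-ups are done.

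**The concern.** The outcome is counted from participation and its data source is counted from baseline. Because training follows baseline, the second clock runs out before the first reaches 12 months. No analysis can supply the missing visit, so this is more than a detail left to a statistical analysis plan.

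If the table is followed as written, the trial would report durability of advocacy 12 months after training from data that stop earlier. Section D.2.3 gives sustainability, including that of advocacy, as one reason for the Sustainment phase, so clinics and policymakers may rely on the stated horizon.

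**Working it through.** **Inputs**

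- Last index survey: 12 months (52 weeks) after baseline (D.2.2.1; section F, part I).
- Order: baseline, then randomization, then sessions (D.2.2.1).
- Session span: seven weekly sessions, so 6 weeks from first to last, or 7 weeks counted as a block (D.2.2).
- Wait from baseline to first session: not stated. Recruitment "will span 8 weeks (5 index and 14 alters per week) at each site" and the intervention is given in groups of 10, so I take 0 to 8 weeks as an assumption.
- Outer limit for training index participants: the first 6 months of implementation (D.2.2).

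**Formula**

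Months from last session to last survey = (52 − wait − span) ÷ (52/12), with wait and span in weeks.

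| Case | Weeks after last session | Months |
|---|---|---|
| No wait, 6-week span (the maximum) | 52 − 0 − 6 = 46 | 10.6 |
| No wait, 7-week block | 52 − 0 − 7 = 45 | 10.4 |
| 4-week wait, 7-week block | 52 − 4 − 7 = 41 | 9.5 |
| 8-week wait, 6-week span | 52 − 8 − 6 = 38 | 8.8 |
| 8-week wait, 7-week block | 52 − 8 − 7 = 37 | 8.5 |
| 8-week wait, a site's two groups in sequence (14 weeks) | 52 − 8 − 14 = 30 | 6.9 |
| Last session 6 months after a woman's baseline | – | 12 − 6 = 6.0 |

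The 12 months in Table 2 are not reproduced in any case. The maximum of 10.6 months does not depend on the assumed wait, because it sets the wait to zero.

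**Counting from the first session instead.** With a wait of 0 to 8 weeks, the survey falls (52 − 8) ÷ (52/12) = 10.2 to 12.0 months after session 1. The value 12.0 requires session 1 on the day of baseline.

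**When a survey would have to take place.** Twelve months after the last session is month 12 + 6 ÷ (52/12) = 13.4 after baseline with no wait and a 6-week span. It is month 12 + 15 ÷ (52/12) = 15.5 with an 8-week wait and a 7-week block. If the groups run in sequence, it is month 12 + 22 ÷ (52/12) = 17.1. No such visit is scheduled.

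**Other women.** Controls have no survey after training. For Sustainment-phase clients, D.2.3 plans clinic records and focus groups but no advocacy survey.

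**Recall period (conditional).** The network section asks about advocacy "with the specific alter in the past 6 months". If those items are used for this outcome, the month-12 answer covers months 6 to 12 after baseline. The start of that window is the gap above minus 6 months: 8.5 − 6 = 2.5 to 10.6 − 6 = 4.6 months after the last session, under the assumed wait.

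**The case against.** The strongest reply is that the cell is loosely worded and simply means the month-12 follow-up. The text below the table promises only that the follow-up surveys will inform sustained engagement, without a horizon measured from training. Advocacy at month 12 is observed, and this is one row of a descriptive implementation framework. Much of this stands: the outcome is secondary, and advocacy by intervention women some months after training will be measured. But if month 12 is meant, the cell is wrong. The two clocks differ by at least 6 weeks (1.4 months), and by 15 weeks (3.5 months) with an 8-week wait and a 7-week block.

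Three stronger readings are tempting, and the protocol does not support them.

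- A reader might infer that a woman who stopped advocating shortly after month 6 would be scored as sustaining it. The 6-month recall is stated only for the alter-specific network items. The 6-item general advocacy scale has no stated recall period, the Maintenance row names neither measure, and how sustained advocacy is scored is not given.
- A reader might take 8.5 to 10.6 months as the trial's actual follow-up after training. It rests on the assumed wait; sequential groups or late delivery would shorten it to 6.9 or 6 months.
- A reader might conclude that no information of any kind exists 12 months after participation. Focus groups ask GC-CCP participants about advocacy, and recorded screening referrals are checked for their names. Neither is the source named for this row, and neither is timed to 12 months per woman, but both could yield some later information.

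**Conclusion.** The point holds in this form: the stated horizon cannot be reached with the stated source. That follows from the order of baseline, randomization and sessions, and needs no assumption about the wait. The month-12 survey is at most about 10.6 months after the last session. The 8.5 to 10.6 month range is conditional on a 0 to 8 week wait with a 6- to 7-week span, and every other timing examined is also short of 12 months. The recall issue is secondary and arises only if the alter-specific items are used. The error affects how a secondary implementation outcome is labelled and interpreted; it does not touch alter screening or the sample size. It should be corrected, because the label as it stands would overstate how long advocacy was shown to last.

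**What to change.** - In Table 2, restate the outcome as advocacy reported at the month-12 post-baseline follow-up among intervention index participants.
- Compute each woman's time from last session to the month-12 survey from the session dates that the chart-abstraction paragraph of D.2.3 already has clinics record. Report its distribution beside the outcome, rather than writing an assumed range into the protocol.
- Make no claim of maintenance 12 months after participation.
- State which advocacy measure defines the outcome. If it is the alter-specific network items, say that the month-12 answer describes months 6 to 12 and not the state at month 12.

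The cost is a change to one table cell and one derived variable, with no new visit. The downside is a shorter stated horizon. If 12 months after participation is truly wanted, the only route is an added index survey at about month 13.4 to 15.5 after baseline (later if groups run in sequence), which is a real extra cost.
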